### Criteria for discontinuing or modifying allocated interventions {11b}

By the end of the randomization process that will allocate all participants to one of the two groups (i.e., control vs intervention), modifying allocated interventions for a given trial participant will not be allowed, except if the participant request is based on a specific health condition that interferes with the study. But these situations will be kept to a minimum.

### Strategies to improve adherence to interventions {11c}

Initially, a psychoeducational session regarding the independent benefits of reducing and interrupting sitting with standing will be given. Besides raising information and literacy, this type of strategy (i.e., educational seminar) has been found to facilitate behavior change in a similar setting [50]. Furthermore, this psychoeducational session will also be given to the control group, highlighting the importance of their participation in the trial (description of how important RCTs are for science will be embedded in the information provided) and reducing the risk of dropout. Control group will also be provided with the intervention (waiting-list group) after the end of the intervention group; thus, it is important to raise early awareness (via the initial session) of the importance of these types of interventions. To enhance desk use, participants will also be given the following: (i) a demonstration of how their desk works; (ii) information on the correct ergonomic posture; and (iii) guidance on gradually building up standing time, as evidence suggests that behavioral feedback and regular contact with research staff are key elements of change [50].

Finally, a theory-based system of prompts will be developed and offered to the participants, assuring contact and motivational nudges throughout the intervention period (for detail, see “Intervention description {11a}”).

In order to gain understanding of participant experiences with the intervention program, two courses of action are planned, both allowing not only to gain in-depth understanding of participants’ barriers and facilitators, but also to help in the refinement of the intervention for future deliveries:(i)Focus groups with a subsample of participants, at the middle of the intervention period, will also be conducted, allowing the participants the opportunity to voice their experiences concerning the use of the new desk (e.g., interest, utility vs. the barriers for use), and interest and usefulness of the intervention contents on the website and team support (e.g., sufficient? Other contents/needs to be addressed)(ii)Insights from the participants will be collected after the initial psychoeducation session, via an open-ended form. This will inform future applications of the intervention. The open-ended form will allow us to check if the information was useful and stimulating and if other contents should be addressed.

### Relevant concomitant care permitted or prohibited during the trial {11d}

Apart from the type of desks at the workplace, no control will exist regarding potential extra strategies that both groups can develop outside this context. However, the participants will be asked about other potential strategies they developed during the study on the second evaluation moment.

### Provisions for post-trial care {30}

We do not expect any harm from this intervention, as we are providing the opportunity for both groups to experience working on a sit-stand desk, without a mandatory amount of change. Regulation of the amount of sitting time replaced by standing will be settled by each participant, informed by information provided in terms of safety and progression given in the initial psychoeducational session and at the time of desk installation. To enhance the internalization of the new habits of breaking sitting time potentially raised by the sit-stand desk, motivational prompts to enhance autonomous motivation and self-regulation in the long term (after intervention-end) will also be provided.

### Outcomes {12}

#### Primary

The primary outcomes of SUFHA are the sedentary and PA-related outcomes (e.g., minutes of SB/day, minutes of sitting time/day, minutes of standing time/day, sit-to-upright transitions/day, number of steps, among others), which will be objectively assessed with 24-h monitoring using the ActivPAL for 7 consecutive days. Changes in these parameters are the main goal of the current RCT (i.e., effectiveness). More details regarding the assessment that generate these outcomes can be found in the “Data collection and management” section. These outcomes will be measured at baseline (i.e., a week within the 30 days prior to the installation of the sit-stand desks), 2nd moment (i.e., final month of intervention), and 3rd moment (i.e., final month of follow-up). Additionally, in the third month of intervention, all participants will be challenged to use the ActivPAL. Although this assessment moment is not mandatory, we expect a significant adherence to this challenge.

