### Sample size {14}

For cluster size and number calculation, we assumed that participants within the same workplace (cluster) would be independent, and therefore, an intra-cluster correlation of 0.01 will be used. Considering the main outcome of the present intervention (i.e., sitting time) and using an effect size of 0.80, the total number of participants for between-group analyses (control and intervention groups) with a power of 0.80 and a significance level of 0.05 (two-tailed test) would be 34 participants. Assuming a 20% dropout, we will conservatively recruit a total sample size of 40 participants (i.e., 20 controls and 20 in the intervention group).

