## Data collection and management

### Plans for assessment and collection of outcomes {18a}

#### Primary data collection

##### Sedentary and PA pattern assessment

We will collect sedentary and PA pattern data derived from an ActivPAL inclinometer/accelerometer monitor (model ActivPAL4; PAL Technologies Ltd., Glasgow, UK), while using the CREA (v1.3) classification algorithm that allows to distinguish non-wear, lying/sitting, standing, cycling, seated during transport, and stepping time as well as the number of steps and stepping cadence. The ActivPAL combines the information from an inbuilt inclinometer and accelerometer and is the reference objective method for monitoring sedentary activity and transitions from and to this behavior among researchers. Due to its position on the thigh, the ActivPAL permits the distinction between standing (vertical position) from sitting or lying (horizontal position), and the accelerometer data allows to distinguish stationary upright activities (i.e., standing) from upright activities with movement (i.e., stepping). The following variables will be calculated from the device:Mean minutes spent sitting,Mean minutes spent standingMean minutes spent steppingMean number of sit-to-upright transitionsMean minutes spent in prolonged (e.g., bouts of ≥30 min) sittingMean minutes spent sleeping

These variables will be calculated across the total waking day. Participants will wear the device on their right thigh 24 h/day for 7 days at baseline, repeating this assessment at the end of the intervention (after 6 months), and after the follow-up period (after 9 months). The 24 h/day wear period will allow to also collect data on sleep quantity.

More information regarding the procedures related to ActivPAL application are stated in the “Procedures” section.

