## Statistical methods

### Statistical methods for primary and secondary outcomes {20a}

Statistical analysis will be performed using PASW Statistics for Windows version 28.0 (SPSS Inc., an IBM Company, Chicago IL, USA). Data will be analyzed for those having completed pre–post test data and using an intention-to-treat analysis. Baseline differences between the intervention and control group will be examined using independent samples *t*-tests. If exploratory analysis reveals a non-normally distribution for some variables, it will be alternatively used with the non-parametric tests. Repeated measures ANOVA, with time (baseline-M0, M1, and M2) as within-subjects factor and intervention condition as between-subjects factor, will be conducted to evaluate the effects of the intervention on primary and on secondary outcomes. Statistical significance will be set at *p* < 0.05.

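### The protocol gives three different accounts of its primary outcome and sizes the trial on only one measure, sitting time

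*Protocol article*

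**What the plan says.** Four places in the protocol article bear on this.

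- **Outcomes {12}, Primary.** The primary outcomes are plural and given by example: "The primary outcomes of SUFHA are the sedentary and PA-related outcomes (e.g., minutes of SB/day, minutes of sitting time/day", followed by "minutes of standing time/day, sit-to-upright transitions/day, number of steps, among others". Five measures are named. The section says that change in these measures is the trial's main goal and refers to the data collection section for detail.
- **Plans for assessment and collection of outcomes {18a}, Primary data collection.** "The following variables will be calculated from the device": minutes sitting, standing, stepping, in prolonged sitting and sleeping, and the number of sit-to-upright transitions. That is six variables. The cut-off for prolonged sitting is itself only an example (bouts of 30 minutes or more).
- **Sample size {14}.** "Considering the main outcome of the present intervention (i.e., sitting time) and using an effect size of 0.80", the total "with a power of 0.80 and a significance level of 0.05 (two-tailed test) would be 34 participants". No other outcome enters the calculation.
- **Statistical methods {20a}.** One repeated measures ANOVA, with times M0, M1 and M2 and the factor group, is used for primary and secondary outcomes alike. "Statistical significance will be set at" p < 0.05, with no distinction between outcomes.

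Objectives {7} places the effectiveness comparison after 6 months of intervention.

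**The concern.** A superiority trial needs one identifiable primary test, or a closed set of tests with a stated rule for success. Here the reader cannot tell whether the primary outcome is one measure, five, six, or more. The sizing treats sitting time as the outcome that decides the trial, while the Outcomes section gives the same rank to standing, transitions, steps and unnamed others.

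The definition of the primary outcome belongs in the protocol, and the article does not merely shorten it: it states versions that disagree. A null result on sitting time could sit beside a significant result on standing time or transitions. Under the Outcomes section that second result would count as primary, although the power statement does not cover it and no error rate has been set for the set of measures.

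**Working it through.** **1. The plan's own figure.** The protocol states no error rate for the primary set. Its only related figure is 34 participants for sitting time. From the stated inputs (standardised effect 0.80, two-sided 0.05, power 0.80), the normal approximation gives 2 × (1.960 + 0.842)² / 0.80² = 24.5, so 25 per arm. The exact two-sample t-test gives 26 per arm, 52 in total. With 17 per arm the t-test has 62% power. The stated inputs alone therefore do not reproduce 34. Unstated assumptions come close: adjustment for a baseline measure correlated at about 0.6 gives 34. This is a separate matter and the present point does not depend on it. What matters here is that 34 refers to sitting time alone.

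**2. The lists side by side.**

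| Measure | Outcomes {12} | Data collection {18a} | Sample size {14} |
|---|---|---|---|
| Total sedentary time | yes | – | – |
| Sitting time | yes | yes | yes |
| Standing time | yes | yes | – |
| Sit-to-upright transitions | yes | yes | – |
| Number of steps | yes | – | – |
| Stepping time | – | yes | – |
| Prolonged sitting | – | yes | – |
| Sleep | – | yes | – |
| Unnamed others | yes | – | – |

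Three measures are common to the first two lists. Their union is 5 + 6 − 3 = 8. Only sitting time appears in all three columns.

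**3. Chance of at least one false positive.** Assume one test per measure at 0.05, no true effect on any measure, and success claimed if any one is significant. For k independent tests this is 1 − 0.95^k. For tests with common correlation ρ, write Z_j = √ρ·G + √(1−ρ)·E_j with G and E_j independent standard normal, and compute P(any |Z_j| > 1.96). The correlations are assumptions, since the protocol gives none.

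| k | ρ = 0 | ρ = 0.5 | ρ = 0.7 | ρ = 0.9 |
|---|---|---|---|---|
| 5 | 22.6% | 18.3% | 14.8% | 10.2% |
| 6 | 26.5% | 20.7% | 16.4% | 10.8% |

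Divided by 5%, these run from 2.0 (k = 5, ρ = 0.9) to 5.3 (k = 6, ρ = 0). An assumed unequal pattern for the five named measures (total sedentary and sitting time 0.95, each with standing −0.85, weaker links elsewhere) gives 16.6%, or 3.3 times nominal.

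**4. What keeping several primaries would cost.** Five co-primaries with Bonferroni are each tested at 0.05/5 = 0.01. At effect 0.80 a t-test then needs 39 per arm (78 in total) for 80% power. With 17 per arm it has 36% power, against 62% at 0.05. These figures ignore clustering.

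**The case against.** **The list may not really be open.** The Outcomes section refers to the data collection section, which gives six variables, and much of the mismatch is between close relatives: total sedentary time and sitting time, steps and stepping time. This stands in part and makes the disagreement smaller than a count of eight suggests. It does not remove it, because prolonged sitting is defined only by example and the sample size section still names a single outcome.

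**Sleep.** A reader might count sleep as primary because it is listed under primary data collection. The documents do not support that firmly. The Outcomes section limits the primary set to sedentary and activity measures, and the data collection section presents sleep as something that 24-hour wear also provides. Five measures is the safer count.

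**The multiplier.** A reader might state the inflation as a fixed three to five times. That rests on unstated correlations of about 0.7 or less. The upper end needs near-independence, which is implausible for measures that share one 24-hour day, with prolonged sitting a part of sitting time. At 0.9 the factor is about 2.

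**Three visits.** A reader might infer that three time points multiply the tests further. The plan fits one model per outcome with time as a factor and announces no test at each visit. Objectives {7} already ties effectiveness to 6 months.

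**No rule that any one measure suffices.** The protocol states none, and multiplicity rules are often left to an analysis plan that is not shown. This is fair. The point therefore rests on the conflict between sections, and the error rates are conditional.

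**Conclusion.** The point holds as a conflict within the protocol. Outcomes {12}, data collection {18a} and Sample size {14} give incompatible accounts of what is primary, and the analysis applies 0.05 to every outcome. Followed as written, the superiority claim has no controlled error rate, and the stated power applies to sitting time only.

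The size is conditional: roughly 10% to 26.5% instead of 5% for five or six measures, if success on any one would be claimed and the correlation between tests lies between 0.9 and 0. Strong correlation is likely for several of these measures, so the top of the range should not be quoted alone. The textual conflict needs correcting whatever the multiplier.

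**What to change.** By a dated amendment made before any post-baseline outcome data are analysed:

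- Name mean waking sitting minutes per day at the end of the 6-month intervention (M1) as the single primary outcome. Measure and time point are both already in the protocol: sitting time is the sizing outcome, the data collection section computes it over the waking day, and Objectives {7} sets the 6-month comparison.
- Make standing time, stepping time or steps, sit-to-upright transitions and prolonged sitting (with a fixed bout length) a closed list of secondary outcomes. Sleep should also be non-primary.
- Either adjust the secondary activity measures by Holm's method, or report them with confidence intervals and no confirmatory claim.
- Use the same definition in Outcomes {12}, data collection {18a}, Sample size {14} and Statistical methods {20a}.

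With one primary test the multiplicity among measures disappears and the sizing assumptions are unchanged.

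The cost is more than wording. The stated aim covers both the quantity and the accumulation pattern of sedentary time, and the pattern measures would lose primary status. A short closed co-primary set with adjustment would keep them, at the loss of power shown above. Trial status reports that recruitment has ended and the intervention is running, and participants and staff are unblinded after baseline. The change is therefore a post-enrolment revision of the primary outcome, and it must be dated, justified and reported as such.

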#### Secondary

The secondary outcomes of SUFHA are body composition (i.e., % of fat mass and fat-free mass, both estimated based on bioimpedance), body mass index (BMI), and waist circumference, all objectively assessed. Postural inequalities based on the analysis of two photos. The Data collection and management section provide more details regarding the assessments that generate these outcomes.

SUFHA also aims to explore secondary outcomes, such as eventual changes in medication, and some psychosocial outcomes, such as overall and work-related fatigue, overall discomfort, life/work satisfaction that comprises four domains (i.e., physical, psychological, environmental, and social), and quality of life. Eating-related habits/behaviors will also be assessed as secondary outcomes, generating individual parameters and an overall score of adherences to the Mediterranean diet and specific behaviors such as breakfast consumption, skipping meals, fast food consumption, homemade meals, take-away meals, and finally eating behavior traits (i.e., emotional eating, intuitive eating, eating restriction, flexible restraint, external eating, and uncontrolled/disinhibited eating). All secondary outcomes will also be measured at baseline (i.e., month before starting the intervention), 2nd moment (i.e., final month of intervention), and 3rd moment (i.e., final month of follow-up).

### Participant timeline {13}

The time schedule of enrolment, interventions, assessments, and visits for participants are presented in a diagram (see Fig. 1). All participants will enter the study and be assessed at the same time points.

**Fig. 1 Fig1:**
[figure not shown]
Flow diagram of enrolment, interventions, assessments, and visits for participants

### Sample size {14}

For cluster size and number calculation, we assumed that participants within the same workplace (cluster) would be independent, and therefore, an intra-cluster correlation of 0.01 will be used. Considering the main outcome of the present intervention (i.e., sitting time) and using an effect size of 0.80, the total number of participants for between-group analyses (control and intervention groups) with a power of 0.80 and a significance level of 0.05 (two-tailed test) would be 34 participants. Assuming a 20% dropout, we will conservatively recruit a total sample size of 40 participants (i.e., 20 controls and 20 in the intervention group).

### Recruitment {15}

We will use different recruitment strategies to match preferences. These will include institutional emails and a project website created with all the information about the project. Also, posters will be created by a professional design team for recruitment and spread out on the University campus. Finally, face-to-face may complement recruitment to attain the aimed number of participants. Based on the average interest rates reported in previous studies assessing the impact of sit-stand desks on SB, the expected proportion of participants interested in taking part in a trial of sit-stand desks at work is 37% of the office workers [62]. All the participants indicating an interest in taking part in the trial will be visited by a researcher who will assess their workspaces for desk installation suitability and 40 participants will be randomized to either the use of sit-stand desks at work for 6 months (i.e., intervention group) or a control group that will only receive the sit-stand desks after the intervention period (i.e., during the 3 months of follow-up).

## Assignment of interventions: allocation

### Sequence generation {16a}

After baseline data collection, cluster randomization using a list randomizer (www.random.org) will be performed by a researcher not involved in recruitment or data collection. The randomization and group allocation process will be made using the different sites as the unit of randomization, to reduce the risk of the intervention being contaminated. A total of 40 office-based workers from different sites will be randomized into two groups: 20 participants to the control group without sit-stand desks and 20 participants to the intervention group with sit-stand desks at work for 6 months. The randomization will consider that control and intervention groups can be matched in some key characteristics, such as the number of transitions from sit to stand and the overall time spent in SB, the BMI, and age. Finally, the randomization will consider if the participants can observe each other from their workstations. In that case, they will constitute a cluster and be randomized as such instead of being randomized individually.

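### The outcome model uses baseline only as a level of time; taking the 6-month value with baseline as a covariate would be more precise and would fit the intended matching

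*Protocol article*

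**What the plan says.** Allocation (Sequence generation {16a}) takes place once the baseline measurements are complete, by this route: "cluster randomization using a list randomizer (www.random.org) will be performed by a researcher not involved in recruitment or data collection". The same section adds "The randomization will consider that control and intervention groups can be matched in some key characteristics", with the examples "such as the number of transitions from sit to stand and the overall time spent in SB, the BMI, and age". It gives no algorithm, strata or tolerance for the matching.

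For analysis (Statistical methods {20a}), the model is "Repeated measures ANOVA, with time (baseline-M0, M1, and M2) as within-subjects factor and intervention condition as between-subjects factor". It serves both sets of outcomes, and no covariate is named. The section also plans a t-test comparison of the arms at the start ("Baseline differences between the intervention and control group will be examined using independent samples"), and it attaches no consequence to the result.

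For size (Sample size {14}), "Considering the main outcome of the present intervention (i.e., sitting time) and using an effect size of 0.80", with power 0.80 and two-sided 0.05, the section states 34 participants. With an assumed 20% dropout it recruits 40. It claims no gain from matching or from adjustment, and it gives no correlation between baseline and follow-up.

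**The concern.** The design and the analysis treat the same variables differently. Time in sedentary behaviour, transitions, BMI and age are thought important enough to steer the allocation, but the model has no term for age or BMI. It uses baseline sedentary time and transitions only by differencing, when those are themselves the outcomes.

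Two consequences follow. First, differencing subtracts the whole baseline value, whereas regression subtracts only the part that predicts the 6-month value. Unless the correlation is close to 1, differencing leaves more noise. Second, if allocation does balance the arms on baseline, the treatment estimate varies less than an unadjusted standard error assumes. The test then rejects less often than 5% under the null. In a trial of 40 people that expects to lose one in five, this avoidable loss of precision matters.

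**Working it through.** **Inputs.** From Sample size {14}: effect size 0.80 (read as a standardised mean difference, since the type is not stated), two-sided 0.05, 40 recruited, 20% dropout. Completers: 40 × 0.8 = 32, or 16 per arm. The baseline-to-6-month correlation r is not in the protocol, so r = 0.3 to 0.8 is assumed. Equal variance at the two times and no clustering are also assumed.

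**The plan's own figure.** A two-sided t-test at d = 0.80 needs 52 participants in total for 80% power (exact noncentral t; 50 by the normal approximation). With 34, power is 62%. The stated 34 is not reproduced from the stated inputs. That is a separate matter, used here only to show that there is little power to spare.

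**Variance of the treatment contrast**, relative to an unadjusted 6-month comparison:
- change score: 2(1 − r)
- 6-month value adjusted for baseline: 1 − r²

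Their ratio, adjusted over change, is (1 − r²) / [2(1 − r)] = (1 + r)/2. This is below 1 for every r below 1, so adjustment has the smaller variance throughout.

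**Power.** The noncentrality is 0.80 × √(32/4) / √(variance factor) = 2.263 / √(variance factor). Degrees of freedom are 30 for the change score and 29 with one covariate.

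| r | change factor | adjusted factor | power, change | power, adjusted |
|---|---|---|---|---|
| 0.3 | 1.40 | 0.91 | 46% | 63% |
| 0.5 | 1.00 | 0.75 | 59% | 71% |
| 0.6 | 0.80 | 0.64 | 69% | 78% |
| 0.7 | 0.60 | 0.51 | 81% | 86% |
| 0.8 | 0.40 | 0.36 | 93% | 95% |

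Two further covariates that explain nothing (27 degrees of freedom) would cost about 0.2 points: at r = 0.5, 71.4% becomes 71.2%.

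**Type I error of the change-score test if balance on baseline were perfect.** The real variance is then proportional to 1 − r², while the test uses 2(1 − r). The actual level is 2[1 − Φ(1.96 / √((1 + r)/2))]:
- r = 0.3: 1.96/√0.65 = 2.43, giving 1.5%
- r = 0.5: 1.96/√0.75 = 2.26, giving 2.4%
- r = 0.6: 1.96/√0.80 = 2.19, giving 2.8%
- r = 0.7: 1.96/√0.85 = 2.13, giving 3.4%

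**Simulation check.** With 34 participants, individual randomization within pairs matched on baseline, and 8,000 runs, the type I error of the change analysis was 1.8%, 2.7% and 3.9% at r = 0.3, 0.5 and 0.7. The baseline-adjusted analysis stayed at about 5% (4.9%, 5.1%, 5.5%). Power was 48% vs 66%, 63% vs 75% and 86% vs 89%. The direction agrees with the formulas. The conservatism is slightly milder because pairing does not give perfect balance.

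**The case against.** **Baseline is not ignored.** This is correct. Baseline is a level of the time factor, so group-by-time removes the outcome's own baseline by differencing. A reader might infer from the missing covariates that the analysis makes no use of the matching variables. That holds only for age and BMI in the models for the sedentary and activity outcomes.

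**The gain depends on an unknown correlation and on a simplified contrast.** This also stands. At r = 0.8 the gain is about 2 points. The calculation covers the baseline-to-6-month contrast without clustering, not the full three-level time factor. What remains is that adjustment has the smaller variance at every r below 1.

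**Covariates can be left to an analysis plan.** Often so, but the article names a specific model and its factors. The point concerns that choice of model, not a missing list.

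**A list randomizer need not conflict with matching.** It could be applied within matched sets of sites, or redrawn until a balance criterion is met. The text does not say, so this is an unclear mechanism rather than a proven contradiction.

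**The baseline t-tests select covariates.** A reader might infer this, but the protocol says only that differences will be examined. Keeping or dropping those tests is a reporting matter.

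**A small trial with few clusters cannot carry many covariates.** This is fair, and it limits the fix to a short list.

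**Conclusion.** The point holds in a limited form. The stated model uses none of the intended matching variables as a covariate, and it handles the outcome's baseline by differencing, which is less precise than adjustment. At d = 0.80 with 32 completers the loss is about 17 points of power at r = 0.3, 12 at 0.5, 9 at 0.6, 6 at 0.7 and 2 at 0.8. With perfect balance on baseline, the nominal 5% change-score test would run at about 1.5% to 3.4% for r = 0.3 to 0.7, and the conservatism fades as r rises. These figures assume equal variances, no clustering and a correlation that the protocol does not give. The degree of balance that allocation would achieve is also unknown.

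A reader might go further and say that the trial forfeits power its sample size had already counted on. Sample size {14} does not support this, because it builds in no gain from matching or adjustment. An adjusted analysis at r = 0.6 would happen to reach 80% power with 34 participants, but the section states neither adjustment nor a correlation. The remedy improves an analysis that would otherwise be wasteful; no bias in the treatment estimate has been shown.

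**What to change.** In Statistical methods {20a}, make the primary analysis the 6-month (M1) value, with the baseline value of the same outcome as a pre-specified covariate. Use a model that accounts for the randomized clusters. Add age and BMI if they are in fact used to balance the allocation. Fix the list in advance and keep it short, because the number of clusters is not given and between-cluster degrees of freedom may be scarce.

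In Sequence generation {16a}, make the matching sentence agree with the list-randomizer allocation actually used: either say how balance was imposed, or remove the sentence.

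The cost is a change of analysis wording and one to three degrees of freedom. Baseline outcome values, age and BMI are already collected, so no new data are needed and the change can be made although recruitment has closed.
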